## Abstract

**Background:**

Multimodal analgesia is achieved by combining different analgesics and different methods of analgesic administration, synergistically providing superior pain relief when compared with conventional analgesia. Multimodal analgesia can also result in reductions in the side effects and complications of analgesia, thereby improving patient safety. Preventive analgesia, treatment before initiation of the surgical procedure, has a potential to be more effective in reducing pain sensitization than treatment initiated after surgery. Multimodal analgesia that includes prophylactic administration of selective cyclooxygenase-2 (COX-2) inhibitors can improve postoperative pain and reduce opioid analgesic consumption after total knee arthroplasty (TKA). However COX-2 inhibitors are not approved for use as preventive analgesia in Japan. Thus, assessing the effectiveness of COX-2 inhibitors during the early postoperative period is important to establish clinical practice guidelines in Japan. This study was designed to examine the effects of celecoxib administration immediately after surgery, in addition to multimodal analgesia, on postoperative pain management after TKA.

**Methods/Design:**

This randomized, prospective, open-label controlled study will include 120 patients undergoing unilateral TKA. All patients will routinely receive single injections of femoral and sciatic nerve blocks, along with postoperative patient-controlled analgesia (PCA) with fentanyl. Patients will be randomly assigned to receive or not receive immediate postoperative administration of celecoxib. The primary outcome is a visual analog scale (VAS) pain score the second day after surgery. Secondary outcomes include opioid consumption, VAS pain score for 7 days after surgery, range of knee motion, evaluation of sleep quality, overall evaluations by patients and physicians, rates of postoperative nausea and vomiting, and consumption of rescue analgesics.

**Discussion:**

The objective of this study is to evaluate the effects of celecoxib administration immediately after surgery on pain after TKA surgery. A randomized controlled trial design will address the hypothesis that administration of oral celecoxib immediately after surgery, along with multimodal analgesia that includes peripheral nerve block and PCA, could reduce VAS pain score after TKA surgery.

**Trial Registration:**

UMIN-CTR 000014624 (23 July 2014)

## Background

Surgical procedure could cause noxious stimulation. Many methods have been used to manage pain after surgery, including various drugs, routes of drug administration and medication methods. Recently, patient-controlled analgesia (PCA) has been more widely used because of its therapeutic effects and safety [1]. PCA is a method of allowing a patient with pain to administer his own pain relief. The infusion is controlled by electronically pump, that delivers prescribed amount of analgesic when a patient press a button. Preventing a patient from overdosing analgesics, a dosage and interval of analgesics are programmed. Patients can self-administer drugs whenever they need analgesics, regardless of broad inter-individual differences in demands for analgesia, thus minimizing inter-individual differences in pharmacokinetics and pharmacodynamics.

Multimodal analgesia is achieved by combining different analgesics and different methods of administration, to provide superior pain relief synergistically compared with conventional analgesia [1]. Moreover, rates of side effects and complications of analgesics are reduced with multimodal analgesia, improving patient safety. The updated 2012 American Society of Anesthesiologists practice guidelines for acute pain management during the perioperative period recommend multimodal techniques for perioperative pain management [1].

Surgical noxious stimuli sensitize the nervous system to subsequent stimuli that could amplify pain. Preventive blocking of nociceptive stimuli to the central nervous system is beneficial in attenuating postoperative pain and in reducing the severity of postoperative pain [2]. Preventive analgesia is a concept for reducing this sensitization before the surgical procedure initiates [2]. Preventive analgesia could be more effective than a similar analgesic treatment initiated after surgery. Surgical trauma induces cyclooxygenase (COX) expression and subsequent synthesis of prostaglandins (PGs), which sensitize peripheral nociceptors and cause nociceptive pain. Since non-steroidal anti-inflammatory drugs (NSAIDs) can inhibit COX and inhibit the synthesis of PGs, NSAIDs are widely used to reduce postoperative hyperalgesia [3].

Traditional NSAIDs inhibit both COX-1 and COX-2 isoenzymes. Celecoxib is a selective COX-2 inhibitor shown to be as effective as traditional NSAIDs as an analgesic for acute postoperative pain. Celecoxib has fewer gastrointestinal side effects than traditional NSAIDs, such as loxoprofen, diclofenac and ibuprofen [4–6]. Moreover, celecoxib has no effects on serum thromboxane and platelet functions, suggesting that it may be an effective postoperative analgesic [7].

Studies have suggested that the administration of selective COX-2 inhibitors for preemptive, multimodal analgesia can improve postoperative pain and reduce the consumption of opioid analgesics after total knee arthroplasty (TKA) [8, 9]. In Japan, however, celecoxib, as well as other NSAIDs, has not been approved for use as preemptive analgesia, but only for postoperative analgesia. Assessing the effectiveness of COX-2 inhibitors as a constituent of multimodal analgesia during the early postoperative period is important to establish clinical practice guidelines.

This study was designed to assess the effects of celecoxib administration during the early postoperative period, along with multimodal analgesia, on postoperative pain management after TKA. We hypothesized that the administration of celecoxib immediately after TKA surgery would provide superior postoperative analgesia compared with delayed administration. Our aim is to compare patient-reported visual analog scale (VAS) pain scores, opioid consumption, range of knee motion, sleep quality, rates of postoperative nausea and vomiting, and rescue analgesic consumption in patients who do and do not receive COX-2 inhibitors, as well as to compare overall evaluations by patients and physicians.

## Methods/Design

### Study design

This study is a single-center, randomized, prospective, open-label controlled trial, performed in accordance with the Declaration of Helsinki and approved by the ethics committee of the Tsukuba University Hospital Mito Clinical Education and Training Center, Mito Kyodo General Hospital, University of Tsukuba. Written informed consent will be obtained from each patient prior to enrollment and testing. This study follows the CONSORT statement (http://www.consort-statement.org/). The trial is registered under the University hospital Medical Information Network and clinical trial registry (UMIN-CTR; http://www.umin.ac.jp/ctr/index.htm) 000014624 (23 July 2014). An overview of the trial design is shown in Figs. 1 and 2.

**Fig. 1 Fig1:**
[figure not shown]
Enrollment: flow diagram of the trial design. Abbreviations: TKA, total knee arthroplasty; OA, osteoarthritis; RA, rheumatoid arthritis; PCA, patient-controlled analgesia

**Fig. 2 Fig2:**
[figure not shown]
Allocation: flow diagram of the intervention. Abbreviations: TKA, total knee arthroplasty; PCA, patient-controlled analgesia

### Eligibility and recruitment

Patients undergoing unilateral TKA as a result of osteoarthritis or rheumatoid arthritis will be recruited from the Department of Orthopaedic Surgery and Sports Medicine, Tsukuba University Hospital Mito Clinical Education and Training Center, Mito Kyodo General Hospital, University of Tsukuba. Identified patients will be approached for inclusion into the study based on the inclusion/exclusion criteria described below.

### Enrollment criteria

#### Inclusion criteria

Patients will be eligible for inclusion if they are aged ≥ 20 years, undergoing unilateral TKA in the morning as a result of osteoarthritis or rheumatoid arthritis, can understand and comply with the study protocol, have signed the informed consent document at screening, and have been assessed by the principal investigator and/or co-investigator as eligible for pain control with multimodal analgesia (including femoral and sciatic nerve blocks and PCA fentanyl after TKA surgery).

#### Exclusion criteria

Patients with a history of complications or hypersensitivity to celecoxib, fentanyl or sulfonamides; a serious allergic reaction to any other drugs; aspirin-induced asthma; or gastrointestinal hemorrhage or ulcer will be excluded. In addition, patients will be excluded if they have severe hepatic, renal, or cardiovascular dysfunction; are in a perioperative period of coronary artery bypass surgery; are pregnant, lactating or probably pregnant. Patients with a history of drug abuse will be excluded. In this study, sleep quality will be evaluated. Hypnotic drugs could alter the sleep state. The central nervous system active medicines often alter the occurrence, latency of specific sleep and dream state, with either therapeutic intent or side effects [10]. In addition, benzodiazepines are rapid eye movement (REM) sleep-suppressant medications, and could induce a withdrawal syndrome with REM rebound [10]. Therefore, those who take or will take a hypnotic drug from 2 days before surgery to final evaluation will be excluded, although ultrashort-acting hypnotic drugs, including triazolam, zopiclone and zolpidem tartrate, are permitted until surgery.

### Randomization

The objective of this study is to evaluate the effects of additional postoperative celecoxib administration on pain after TKA surgery. All patients will routinely receive a combination of femoral/sciatic nerve blocks and postoperative fentanyl PCA and be randomized using a computer-generated list to one of two groups, one of which will receive immediate postoperative celecoxib (*celecoxib group*), whereas the other will not (*control group*).

A computer-generated scheme will randomize patients in a 1:1 ratio matched by illness, either osteoarthritis or rheumatoid arthritis. Patients will be assigned to either intervention or control group within 14 days before surgery. Randomization will be performed centrally by Tsukuba Critical Path Research and Education Integrated Leading Center (CREIL center), Tsukuba Critical Path Research and Education Integrated Leading Center (CREIL center) Tsukuba Clinical Research and Development Organization (T-CReDO), University of Tsukuba.

### Intervention plan

#### Dosage, route of administration, and period of investigational drugs

In accordance with the package insert, and as in a previous study [9], the first oral dose of celecoxib will be 400 mg, followed by 200 mg in both the celecoxib and control groups. Patients in the celecoxib group will receive 400 mg celecoxib 2 hours after TKA, followed 6 hours later by 200 mg celecoxib and 200 mg celecoxib twice daily beginning the day after surgery until day 7. Patients in the control group will receive 400 mg celecoxib on the morning of the second day after surgery, which is the day of PCA fentanyl removal, followed 6 hours later by 200 mg celecoxib and 200 mg twice daily until the seventh day after surgery [9].

#### Perioperative analgesia

Surgery will be performed under general anesthesia. After general anesthesia is induced, a single injection of peripheral nerve blocks, consisting of 25 ml of 0.375 % ropivacaine hydrochloride as a femoral nerve block and 25 ml of 0.2 % ropivacaine hydrochloride as a sciatic nerve block, will be administered under ultrasound guidance.

Postoperative analgesia will consist of PCA with fentanyl citrate. At the end of surgery, the PCA pump will be started at a basal rate of 10 μg per hour. An on-demand mode will be programmed, allowing for bolus injections of 15 to 20 μg every 5 minutes, with the maximum basal and bolus doses allowed per hour being 250 μg.

#### Rescue analgesic

Patients who require an additional analgesic after PCA fentanyl removal on the second day after surgery will be allowed a 25 or 50 mg diclofenac sodium suppository. Usage of the rescue analgesic will be recorded.

### Outcomes

#### Primary outcome measure

The primary outcome measure in this study will be patient-reported VAS pain score at 9 o’clock on the second day after TKA. This measure will allows us to identify the effect of early administration of celecoxib (Table 1).

**Table 1 Tab1:** Data collection schedule

	Day before surgery	Day of surgery	Postoperative day(s)				Discontinuance
			1	2	3–6	7	
VAS pain score	●	●^a^	●^b^	●^b^	●^b^	●^b^	●
Fentanyl consumption		●	●	●			
ROM	●			●		●	●
VAS sleep score^c^	●	●	●	●		●	●
SLEEPSCAN™ %	●	●	●	●		●	●
Patient satisfaction						●	●
Evaluation by physician						●	●
PONV		●	●	●	●	●	●
Rescue consumption				●	●	●	●
Adverse events		●	●	●	●	●	●

^a^Two hours after the end of surgery; ^b^9 a.m. before oral administration; ^c^evaluation the next day; % overnight measurement

Abbreviations: VAS visual analog scale; ROM range of motion of the knee; PONV postoperative nausea and vomiting

SLEEPSCAN™ (TANITA Corporation, Japan) is a tool for evaluating sleep quality

#### Secondary outcome measures

For secondary outcome measures, fentanyl consumption through PCA is assessed at 2 days after surgery; VAS pain score is assessed at 9 a.m. each day from 1 to 7 days after surgery; range of motion of the knee joint is assessed at 9 a.m. at 2 and 7 days after surgery; postoperative sleep quality is evaluated at 1, 2 and 7 days; overall patient satisfaction during the period of medication is evaluated at 7 days after surgery; overall evaluation by the physician during the period of medication is assessed at 7 days after surgery; incidence rates of postoperative nausea and vomiting and frequency of taking anti-nausea pills is assessed for the 7 days after surgery; and consumption of rescue analgesics (diclofenac sodium suppositories) after the discontinuation of PCA fentanyl is assessed overall for the 7 days after surgery (Table 1).

Sleep quality at 9 a.m. on postoperative 1, 2 and 7 days will be evaluated by patient-reported VAS sleep disturbance. For objective sleep assessment, sleep latency, sleep efficacy, nocturnal awakening, depth of sleep, body motion, and deep sleep time will be monitored by SLEEPSCAN™ (TANITA Corporation, Japan) [11]. SLEEPSCAN monitors body motion, breathing, and heart rate through the bedding mattress with a water seal and pressure sensor, without the necessity of installing direct sensors, including bioelectrodes, on the human body [11].

### Assessment of safety

Administration of study drugs will be immediately stopped in participants who show relevant deterioration. Severe adverse events, as determined by the Common Terminology Criteria for Adverse Events (CTC-AE) ver. 4.0, will be reported to the principal investigator, who will report any unexpected serious adverse reactions to the institution.

### Data collection

Data collection across time points is shown in Table 1. Data collection is performed by research assistants for VAS pain score, fentanyl consumption, VAS sleep score, SLEEPSCAN, patient satisfaction, PONV, and rescue consumption. Physical therapists will measure knee ROM. Research assistants and physical therapists are independent of the clinical management of the subjects. The collected data will be transferred to the T-CReDO data center as soon as each patient completes the schedules, and will be analyzed by an independent researcher. After collecting data, an independent clinical research coordinator will verify the data collection by confirming medical records. These processes will be unaffected by any researchers.

The validation of collected data for this cohort is important. Previously, patient-reported VAS pain score has been well validated [12–14]. Because of its practicality, reproducibility, sensitivity to treatment effects, and ease of analysis, the VAS pain scale is a powerful research tool in the field of pain research. No significant differences have been observed in VAS pain score for each of the variables including age, sex, and cause of pain [14]. In addition, patients’ satisfaction and sleep quality are also validated previously [11, 15]. Therefore, the collecting data from this study is believed to be validated.

#### Sample size calculation

The primary outcome of this study is patient-reported VAS pain score on the second day after surgery, based on the hypothesis that immediate postoperative administration of oral celecoxib could reduce patient-reported VAS pain score 48 hours after TKA surgery compared with the control group.

Sample sizes are chosen to detect clinically relevant differences using a power analysis based on previously published data evaluating the effect of celecoxib on VAS pain score after TKA [9]. The minimal clinical significance in VAS pain score was defined as the mean difference between current and preceding scores when the subject reported “a little worse” or “a little better” pain [12]. Previous study shows that VAS pain scores 48 hours after TKA surgery were reported to be 21.3 ± 16.8 mm in patients receiving celecoxib plus PCA morphine and 34.3 ± 16.6 mm in patients receiving PCA morphine alone [9]. Based on these findings, we hypothesized that VAS pain score 48 hours after surgery will be 22 mm for the celecoxib group (postoperative oral celecoxib plus nerve block and PCA fentanyl) and 33 mm for the control group (nerve block and PCA fentanyl alone), with a standard deviation set at 20.0 mm and a ratio of patients in the celecoxib to the control group of 1:1. Calculations showed that a sample size of 53 patients per group would provide 80 % power (alpha = 0.05, two-tail) to detect a difference in VAS pain score between the two groups after treatment, and also the minimal detectable change of 10 mm within each group [9]. Assuming a 10 % dropout rate, 60 patients per group, or a total of 120 patients, are required.

### Plan for statistical analysis

The intention-to-treat analysis will be conducted for all patients who underwent randomization. Baseline information on study subjects in two treatment groups such as demographics, preoperative VAS pain scores, ranged of motion and sleep quality will be described. The primary outcome that the differences of VAS pain scores between celecoxib and control groups at the second day after surgery will be analyzed by ANOVA. The secondary outcomes including the pain-medication use, adverse reactions, VAS pain scores, range of motion of knee joint, sleep quality, patient satisfaction, and overall evaluation by physicians after surgery will be analyzed by ANOVA or Chi square test. Nonparametric tests may be used for continuous variables if they are not normally distributed. Between-group comparisons of treatment effect for primary and secondary outcomes, except for pain-medication use and adverse events, will also be conducted with the use of a mixed-effects model, with patient as a random effect and time of assessment (baseline and follow-up days), study group, and baseline values of the outcome as fixed effects.

Significance will be set as *P* < 0.05. All statistical analyses will be performed by using SAS 9.4 (SAS Institute Inc., Cary, NC, USA).

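### The primary day-2 VAS comparison is unadjusted although preoperative VAS is collected and allocation is by diagnosis: a loss of precision, not of validity, that the added mixed model does not recover

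*Protocol article*

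**What the plan says.** In the protocol article, under Plan for statistical analysis, the primary outcome is the difference in VAS pain that "at the second day after surgery will be analyzed by ANOVA". No covariate or stratum is attached to that analysis. Among the baseline data, "preoperative VAS pain scores, ranged of motion and sleep quality will be described"; Table 1 confirms that VAS pain is recorded on the day before surgery.

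The same section adds a second analysis. Comparisons for the primary outcome and most secondary outcomes "will also be conducted with the use of a mixed-effects model, with patient as a random effect". Its fixed effects are assessment time (with baseline counted as one of the times), "study group, and baseline values of the outcome as fixed effects". No group-by-time interaction is listed, and diagnosis is not mentioned.

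Under Randomization, a computer scheme will "randomize patients in a 1:1 ratio matched by illness, either osteoarthritis or rheumatoid arthritis". I read this as stratification by diagnosis.

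The sample size calculation is for an unadjusted two-group comparison: "a sample size of 53 patients per group would provide 80 % power" ("alpha = 0.05, two-tail").

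**The concern.** Two pieces of information that could sharpen the primary comparison are available and are not used in it. Preoperative VAS may explain part of the variation in day-2 VAS. Diagnosis is the factor on which allocation is balanced; if that balance is left out of the analysis, any OA–RA difference stays in the error term.

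The mixed model might seem to supply the adjustment, but as listed it answers another question. A single group term with no group-by-time interaction gives one effect shared by all assessment times, baseline included. Under the dosing section, controls start celecoxib on the morning of day 2, and Table 1 places the VAS reading at 9 a.m. before oral dosing. From day 3 both groups are on the drug. The contrast of interest therefore belongs to the early readings, and averaging it with baseline and the later days dilutes it. The one analysis aimed at day 2 is unadjusted, and the one that is adjusted is not aimed at day 2.

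At stake are the width of the primary confidence interval and some power in a trial planned at about 80%.

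**Working it through.** **Inputs from the protocol article (Sample size calculation).** "22 mm for the celecoxib group" against 33 mm for control, so a difference of 11 mm; SD 20 mm; two-sided alpha 0.05; 53 per group.

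**Reproducing the plan's figure.** Normal approximation: n per group = 2 × (1.960 + 0.842)² × 20² / 11² = 51.9, so 52. The two-sample t-test gives 52.87, so 53, with power 80.1% at 53. The stated figure is reproduced for an unadjusted comparison.

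**Adjusting for preoperative VAS.** The correlation r between preoperative and day-2 VAS is not in the document, so it is an assumption and is run over a range. Residual SD = 20 × √(1 − r²); standard error of the difference = residual SD × √(2/53); power from the two-sample t-test at 53 per group; equivalent gain in patients = 1/(1 − r²) − 1.

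| r (assumed) | Residual SD, mm | SE, mm | Power | Equivalent extra patients |
|---|---|---|---|---|
| 0 | 20.0 | 3.89 | 80.1% | none |
| 0.2 | 19.6 | 3.81 | 81.7% | 4% |
| 0.3 | 19.08 | 3.71 | 83.7% | 10% |
| 0.4 | 18.33 | 3.56 | 86.4% | 19% |
| 0.5 | 17.32 | 3.36 | 90.0% | 33% |

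The one or two degrees of freedom spent on covariates are ignored here; out of about 104 they do not matter.

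**Leaving out diagnosis.** Let p be the share with rheumatoid arthritis and D the OA–RA difference in day-2 VAS; neither is in the document. With exact balance by diagnosis, the share of variance wrongly left in the error term is f = p(1 − p)D²/400. The standard error is too large by 1/√(1 − f) − 1, and the actual type I error is 2 × [1 − Φ(1.96/√(1 − f))].

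- p = 10%, D = 5 mm: f = 0.09 × 25/400 = 0.0056; standard error 0.3% too large; type I error 0.049.
- p = 20%, D = 10 mm: f = 0.16 × 100/400 = 0.04; standard error 2.1% too large; type I error 0.046.
- More extreme, p = 30%, D = 15 mm: f = 0.21 × 225/400 = 0.118; standard error 6.5% too large; type I error 0.037.

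**What the mixed model's group term estimates.** With complete data and one group term common to all times, the coefficient is the average of the group differences over the times in the model. As an illustration with assumed effects, take 11 mm on days 1 and 2 and zero at baseline and on days 3 to 7. The average over the eight assessments is 22/8 = 2.75 mm, against 11 mm on day 2.

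**The case against.** The strongest reply is that nothing promised is lost. Under randomisation the unadjusted comparison is unbiased, the trial was sized for exactly that comparison, and it reaches its stated power. This stands. A reader might infer from the lack of adjustment that the primary analysis is biased or the trial underpowered; the document supports neither.

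A reader might also infer that baseline is ignored altogether. It is not: the mixed model includes it and covers the primary outcome. What remains is that this model, as listed, does not isolate day 2, and that the article does not rank it against the ANOVA.

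The size of the gain is unknown. Preoperative arthritic pain and acute pain two days after surgery, following nerve blocks and with fentanyl PCA, may correlate weakly; at 0.2 the gain is under two points of power. Quoting only the upper part of the range would overstate it.

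The diagnosis component is small. The Data collection section itself reports that VAS pain has not been found to differ significantly by cause of pain, which argues for a small OA–RA gap, and the error is in the conservative direction.

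Nor does a chance imbalance in preoperative VAS pass undiminished into the estimate. Only the regression slope times the imbalance carries over: with equal SDs and r = 0.3, a 5 mm imbalance shifts the estimate by 0.3 × 5 = 1.5 mm, and the unadjusted interval already allows for such variation.

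Finally, a condensed article may leave model terms to an analysis plan that is not shown. That is a fair caution about the ANOVA, which the article does not call one-way. It carries less weight here because the article does list the mixed model's terms, and diagnosis is not among them.

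**Conclusion.** The point holds as a matter of efficiency. The primary analysis as named forgoes a baseline covariate that is already collected and a factor on which allocation is balanced, and the additional model does not make up for this. At 53 per group the forgone power runs from almost nothing (correlation near zero) through 1.6 points (r = 0.2) to about 10 points (r = 0.5). The diagnosis part adds about 0.3% to 2% to the standard error if 10% to 20% of patients have rheumatoid arthritis and the diagnoses differ by 5 to 10 mm, and it makes the test slightly conservative. The correlation, the rheumatoid arthritis share and the OA–RA difference are all assumptions. The reason to include diagnosis is chiefly that the analysis should reflect the randomisation.

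The change is worth making because it is nearly free, not because the planned ANOVA is invalid.

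**What to change.** Make the primary analysis an ANCOVA of the 9 a.m. day-2 VAS with group, preoperative VAS and diagnosis (OA/RA) as terms, and report the adjusted mean difference with its 95% CI. Keep the unadjusted ANOVA as a sensitivity analysis. Add diagnosis to the models for continuous secondary outcomes; the planned chi-square comparisons have no place for a covariate, so this cannot extend to every secondary analysis. If the mixed model is kept in support of the day-2 result, it needs a group-by-time term, a day-2 contrast and diagnosis.

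No new data are required. The cost is about two degrees of freedom and one amendment sentence. The Trial status section says recruitment began in October 2014, and the trial is open-label, so the amendment should be dated and made without knowledge of outcome data.

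### The test for the primary day-2 VAS can be switched on an undefined normality check and is repeated in an unranked mixed model, so the plan does not say which result decides the trial

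*Protocol article*

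**What the plan says.** All the analysis statements are in the protocol article, under Plan for statistical analysis.

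- The primary test is named: "the differences of VAS pain scores between celecoxib and control groups at the second day after surgery will be analyzed by ANOVA".
- A general permission follows: "Nonparametric tests may be used for continuous variables if they are not normally distributed". VAS is a continuous variable and the primary outcome is not excepted. The sentence gives no diagnostic, threshold or replacement test.
- The primary outcome is then compared again: "Between-group comparisons of treatment effect for primary and secondary outcomes, except for pain-medication use and adverse events, will also be conducted" in a mixed model. Besides a random patient effect, its terms are "time of assessment (baseline and follow-up days), study group, and baseline values of the outcome as fixed effects". No group-by-time term is listed.
- One level covers everything: "Significance will be set as" P < 0.05.

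Under Sample size calculation, the trial is sized on means of 22 mm (celecoxib) and 33 mm (control), "with a standard deviation set at 20.0 mm", 80% power and "alpha = 0.05, two-tail".

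**The concern.** Three analyses of the same outcome are possible, and no sentence ranks them. Whether the first gives way to the second depends on the observed distribution, and even then the choice is optional.

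They do not answer the same question. ANOVA compares means at day 2. A rank test compares distributions and gives no estimate in mm of the planned mean difference. The mixed model, without a group-by-time term, gives one group effect averaged over all assessments.

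At stake are which p-value supports the trial's claim, and whether the headline result is the day-2 mean difference that the sample size was built on.

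**Working it through.** **1. Reproduce the sample size.** Inputs from Sample size calculation: difference 33 − 22 = 11 mm, SD 20 mm, two-sided 0.05, power 80%.

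Normal approximation: n = 2 × (1.960 + 0.842)² × 20² / 11² = 51.9, so 52 per group. The two-sample t-test formula gives 52.87, so 53, with power 0.801. This matches the stated 53. Dropout: 53 / 0.90 = 58.9, so 59, against the stated 60. The trial is therefore sized as a comparison of means.

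**2. Is the switch condition likely to be met?** Distance of zero below each planned mean, and the share a normal curve would put below 0 mm:

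| Arm | Mean / SD | Share below 0 |
|---|---|---|
| Celecoxib | 22 / 20 = 1.10 | 13.6% |
| Control | 33 / 20 = 1.65 | 4.9% |

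Scores below 0 cannot occur, so the planning values imply skew or a pile-up at the floor. The protocol gives neither a shape nor a normality test. The simulations (2,000 trials per setting, 53 per arm) therefore assume a 0–100 mm scale, Shapiro-Wilk at 0.05, and a beta, gamma or censored-normal shape.

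| Values used | Rejects in at least one arm | Rejects on pooled residuals |
|---|---|---|
| Planned (22/33, SD 20) | 99.7–100% | 92–100% |
| Cited earlier trial (21.3/34.3, SD about 16.7) | 90–100% | 45–99% |
| Truly normal data, for contrast | 9–10% | about 5% |

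**3. Does the choice between ANOVA and rank test matter?** At the planned values the t-test (identical to a two-group ANOVA) and Wilcoxon disagreed on significance in 4–12% of trials. Under the bounded shapes, power was 0.79–0.82 for the t-test and 0.83–0.94 for Wilcoxon.

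**4. False-positive rate.** Null simulation: 4,000 trials per setting, 53 per arm, mean 33 and SD 20 in both arms, beta or normal shape, baseline plus seven daily scores, assumed between-time correlation 0.3, 0.5 or 0.7. For the mixed model, each patient's average over the eight scores was regressed on group and baseline. Simulation error at 5% is √(0.05 × 0.95 / 4,000) = 0.3 percentage points.

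| Rule | False positives |
|---|---|
| t-test alone | 4.4–5.5% |
| Wilcoxon if Shapiro-Wilk rejects, otherwise t-test | 4.4–5.6% |
| Better of t-test and Wilcoxon | 5.2–6.6% |
| Better of ANOVA and mixed model | 8.4–9.3% |
| Best of all three | 9.1–10.2% |

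For reference, two independent tests at 0.05 would give 1 − 0.95² = 9.75%.

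**5. What the mixed model estimates.** Under Dosage, route of administration, and period, the control group starts celecoxib on the morning of day 2. Table 1 takes the 9 a.m. VAS before the oral dose. From day 3 both arms are therefore on celecoxib. As an illustration only, suppose an 11 mm difference on days 1 and 2 and none at baseline or on days 3–7. The average over eight assessments is then 2 × 11 / 8 = 2.75 mm. If the 11 mm lasted through all seven days it would be 7 × 11 / 8 = 9.6 mm. Neither figure is the day-2 contrast.

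**The case against.** ANOVA is expressly assigned to the primary outcome. The mixed model is introduced with the word also and covers primary and secondary outcomes together, so it reads most naturally as supplementary. A reader might infer that the trial has no named primary test; the text does not support that. The gap is an open switch and an unstated ranking.

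A reader might also infer that the normality switch itself inflates error. It does not: applied as a rule, it stays near 5%. If non-normality is almost certain, the rule amounts in practice to a rank test. The switch does not cost power under skewed shapes either.

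Nor can one say that the mean difference will be dropped. The switch is optional, the normality test and distribution shapes are assumptions of this review, and at the cited trial's values the pooled-residual check rejects in as few as 45% of trials. Reporting a rank test would not stop means being reported as well.

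Finally, Data collection says an independent researcher will analyse the data, and a journal article may leave the diagnostic and the named test to an SAP. Both points carry weight. Independence lowers the risk of opportunistic choice but does not say which result decides. An SAP could settle the ranking, but the rule printed here is discretionary and reaches the primary outcome, so the objection is to what is written and not to missing detail.

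**Conclusion.** The concern holds in a limited form. ANOVA is the named primary test, but it can be replaced at the analysts' option after the distribution is seen, and the comparison is repeated at the same level in a model that does not isolate day 2. Nothing states which result decides.

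The switch condition will probably be met at the planned values if the scores have a plausible bounded shape. With 53 per arm, the comparison of means kept its level and its planned power under the bounded shapes tried, so validity does not require the switch.

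The rise to about 8–10% false positives is conditional. It needs the freedom to claim the better of the ANOVA and mixed-model results, and it rests on the assumed distributions and on correlations of 0.3–0.7. The text does not plan such a choice, but it does not rule it out.

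**What to change.** State that the sole primary analysis, whatever the distribution, is the between-group mean difference in VAS at 9 a.m. on day 2, with its 95% CI, tested at two-sided 0.05. ANCOVA with the preoperative VAS as covariate is preferable, since Table 1 already collects that score. Keeping the stated ANOVA would also close the gap.

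Exempt the primary outcome from the sentence permitting nonparametric tests. Name the Wilcoxon test and the mixed model as sensitivity analyses that cannot replace the primary result.

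The cost is one or two sentences, with no new data and no change to 60 per group. The analysts lose the option of choosing the test after seeing the data. If the scores are skewed they also forgo some power that a rank test might offer (0.83–0.94 against 0.79–0.82 in the simulations).
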